## Abstract

Background: Gambling behaviors among college students are a growing public health concern, with problem gambling rates significantly higher in this population than in the general public. Aim: This study outlines the protocol for a randomized controlled trial (RCT) evaluating the efficacy of RESPONSIBLEPLAY^©^, a Multi-theory Model (MTM)-based intervention designed to promote responsible gambling behaviors. Proposed Methods: The intervention integrates six MTM constructs—participatory dialogue, behavioral confidence, changes in the physical environment, emotional transformation, practice for change, and changes in the social environment—to address the initiation and sustenance of behavior change. College students aged 21 and older, scoring 3 or higher on the Problem Gambling Severity Index (PGSI), will be randomly assigned to either the MTM-based intervention group or a traditional knowledge-based intervention group. The participants will complete surveys assessing PGSI and MTM constructs at pre-test, post-test, and eight-week follow-up. This study aims to provide evidence for the efficacy of theory-driven intervention compared to a knowledge-based approach. Conclusions: If successful, this protocol will establish a robust framework for mitigating gambling-related harm in vulnerable college populations, paving the way for scalable, evidence-based interventions in diverse settings. The findings will contribute to the development of public health strategies that integrate theoretical constructs with practical applications to address high-risk behaviors.

## 1. Introduction

Gambling behaviors among college students have become a significant public health concern, with research indicating that this demographic is particularly susceptible to gambling-related harms [1]. Globally, approximately 10.23% of college students experience problem gambling, while 6.13% meet the criteria for Gambling Disorder (GD)—a prevalence notably higher than that in the general population [2]. Several factors contribute to this heightened risk, including increased independence, peer influence, and expanded access to gambling opportunities, all of which can lead to adverse outcomes such as academic difficulties, financial hardship, and mental health challenges [3]. Despite these risks, interventions aimed at promoting responsible gambling behaviors among college students remain limited in both scope and effectiveness.

This protocol details the implementation of a randomized controlled trial (RCT) to evaluate the efficacy of RESPONSIBLEPLAY^©^, an MTM-based intervention designed to promote responsible gambling among college students. This study addresses a critical gap in the literature by comparing the MTM-based intervention with a traditional knowledge-based approach. The findings will offer valuable insights into the effectiveness of theory-driven behavioral interventions and their potential to reduce gambling-related harm within this high-risk population.

The protocol outlines the procedures for assessing the efficacy of RESPONSIBLEPLAY^©^ in fostering responsible gambling behaviors among college students. Specifically, it aims to determine whether the MTM-based approach leads to significant improvements in gambling behaviors, as measured by the Problem Gambling Severity Index (PGSI) and MTM constructs, compared with a traditional knowledge-based intervention.

By examining the factors influencing gambling behaviors in this population, this research seeks to strengthen the evidence base for designing and implementing tailored interventions to mitigate gambling-related harms. This study’s findings will inform the development of more effective, evidence-based strategies to promote responsible gambling, enhance student well-being, and potentially extend to other at-risk populations.

### Literature Review

The growing popularity of online gambling and emerging gambling platforms has further intensified gambling-related harms, posing new challenges for public health practitioners and researchers. College students frequently participate in various forms of gambling, including sports betting, lottery games, and fantasy sports, often influenced by peer networks and the accessibility of gambling opportunities in their environment [4,5,6]. While previous interventions, such as cognitive behavioral therapy (CBT) and personalized normative feedback (PNF), have shown effectiveness in reducing gambling frequency and associated harms [7,8,9], their theoretical frameworks have often been applied inconsistently, and many lack a fully integrated approach to maximize their impact. This study seeks to address these gaps by establishing a more cohesive theoretical foundation. Left unaddressed, gambling behaviors among college students can escalate into problem gambling or GD, highlighting the urgent need for theory-driven, evidence-based interventions tailored to this population.

The Multi-theory Model (MTM) of health behavior change presents a promising framework for addressing the complexities of gambling behaviors among college students. As a fourth-generation theoretical model, MTM integrates insights from multiple behavioral theories to facilitate both the initiation and maintenance of health behavior change [10,11]. By incorporating all six constructs of MTM—participatory dialogue, behavioral confidence, changes in the physical environment, emotional transformation, practice for change, and changes in the social environment—this framework offers a comprehensive approach to designing targeted interventions that promote responsible gambling behaviors. Its holistic structure effectively addresses the intricate psychological, social, and environmental factors influencing gambling behaviors in this population. By fostering both initial behavior modification and long-term adherence, MTM provides a robust foundation for developing tailored, sustainable interventions that mitigate gambling-related harm among college students. To highlight the distinct contribution of the current study, Table 1 below summarizes how the proposed intervention differs from previously published gambling interventions.

## 2. Materials and Methods

### 2.1. Study Design

This study will implement a three-week, single-blinded educational randomized controlled trial (RCT), followed by an eight-week follow-up phase (ClinicalTrials.gov number: NCT06642155). The RCT design, widely recognized as the gold standard for evaluating intervention efficacy, was selected for its ability to minimize bias and establish causal relationships between the intervention and its outcomes through randomization [12]. To ensure methodological rigor and transparency, this study will adhere to the CONSORT checklist for RCTs [13], maintaining high standards of reporting throughout the research process. Figure 1 presents the CONSORT flow diagram.

To evaluate changes in health behavior among the participants, this study will administer pre-, post-, and follow-up assessments using the Multi-theory Model (MTM) constructs [10] and the Problem Gambling Severity Index (PGSI) [14]. The participants will be randomly assigned to one of two groups: the experimental group, which will receive the RESPONSIBLEPLAY^©^ MTM-based intervention, or the comparison group, which will receive a knowledge-based intervention. Random assignment, a fundamental component of RCTs, ensures that all the participants have an equal likelihood of being placed in either group. This approach minimizes selection bias, enhances the validity of the findings [15], and helps balance both known and unknown confounders between groups. Consequently, any observed differences in outcomes can be confidently attributed to the intervention rather than to pre-existing disparities [15]. Figure 2 presents an overview of the study design for evaluating the efficacy of responsible gambling interventions.

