### 2.4. Study Procedure

Participant recruitment will target college students aged 21 and older at the university. The recruitment efforts will include email invitations that introduce this study and invite eligible students to participate. The intervention sessions will be conducted in person. The participants will be randomly assigned to either the experimental group (RESPONSIBLEPLAY^©^: MTM-based intervention) or the comparison group (knowledge-based intervention) using SAS PROC SURVEYSELECT. Participant data will first be imported from an Excel file, and each participant will be assigned a unique ID. Simple random sampling (SRS) will then be conducted using PROC SURVEYSELECT, ensuring equal probability of assignment to either group. A fixed seed (12345) will be used to ensure reproducibility. The function will generate a selection indicator (Selected = 1 for the experimental group and Selected = 0 for the comparison group), which will be used to assign the participants accordingly. The final randomized dataset, including group assignments, will then be exported for implementation.

The intervention will be conducted over three weeks, with one session scheduled per week. Each session will span three days, offering multiple time slots to accommodate the participants’ schedules. This approach ensures that all the participants receive the same intervention content while allowing flexibility in attendance. The first session (Week 1) will include an orientation, completion of the pre-intervention survey, and the start of the intervention activities. The final session (Week 3) will consist of intervention activities followed by the post-intervention survey.

To enhance attendance and engagement, the participants will receive email reminders before each session. Additional reminders will be sent to the experimental group between sessions and after the intervention to reinforce the practice of responsible gambling behaviors. At the eight-week follow-up, the participants will attend a final assessment session, which will be scheduled in advance. Email reminders will also be sent to maximize participation.

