### 2.6. Strategies to Prevent Cross-Group Influence

To minimize cross-group influence, this study will implement several strategies. Intervention sessions for the experimental and comparison groups will be scheduled separately, and group-specific materials will be clearly labeled and distributed exclusively to each group. The participants will be briefed on confidentiality and instructed not to discuss session content with members of the other group. The research team will actively monitor sessions to ensure adherence to these protocols and address any issues promptly. These measures aim to preserve this study’s integrity and validity.

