### 2.7. Interventions

The experimental group will participate in a three-week intervention based on the MTM of health behavior change [10]. This intervention includes role-playing, psychodrama, journaling, and exploring recreational alternatives to address gambling behaviors. Participants will document their gambling-related activities, physical and emotional challenges, and achievements throughout the program. Each session will last approximately 60 min and be held once per week for three weeks. To encourage participation, the participants will receive a USD 20 gift card after each session and again at the eight-week follow-up.

Session 1: This session explores the pros and cons of gambling, emphasizing how the benefits of responsible gambling outweigh its risks. The participants work on building behavioral confidence, developing plans for responsible gambling, and identifying environmental changes that support responsible gambling practices (Supplement S1).

Session 2: In this session, the participants reflect on their emotions related to gambling and explore techniques for transforming negative emotions into positive ones. They receive guidance on journaling and record-keeping as tools for self-awareness and accountability. Additionally, the participants engage in recreational activities as alternatives to gambling and identify sources of social support that encourage responsible gambling behaviors (Supplement S1).

Session 3: The final session features a guest speaker from the Nevada Council on Problem Gambling, who will provide insights and motivation. The activities focus on initiating responsible gambling behaviors over the next eight weeks and strategies for sustaining them. The participants also receive practical demonstrations of techniques to implement and maintain responsible gambling behaviors long term (Supplement S1).

The comparison group will participate in three knowledge-based sessions, each featuring lectures and presentations focused on gambling behavior (Supplement S2). Each session will last approximately 60 min. At the conclusion of the eight-week follow-up, the participants will receive an incentive (a USD 20 gift card) as a token of appreciation and to support their continued learning. The Table 2 describes the alignment of intervention components with MTM constructs and behavioral outcomes.

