This study relies on the PGSI as one of the key outcome measures. While the PGSI is a widely validated and commonly used instrument, its 12-month recall period may limit its sensitivity to detecting short-term behavioral changes resulting from the intervention. To address this, we will supplement our analyses with MTM construct scores, which are specifically designed to measure short-term behavioral initiation and sustenance. Additionally, we will conduct item-level analyses of the PGSI responses (e.g., related to gambling expenditure, time lost, or emotional impact) to assess whether certain dimensions demonstrate greater sensitivity to short-term change. While the PGSI was selected for its classification utility and comparability across studies, we acknowledge that it is best suited for long-term assessments. Accordingly, we are also exploring the feasibility of a 6- to 12-month follow-up study to better align with the PGSI’s recall window and to assess sustained changes in gambling behavior. This extension will depend on participant retention and funding availability but would provide a more complete evaluation of the intervention’s longitudinal impact.

While simple randomization is used for group assignment, we acknowledge that this method may result in imbalances in baseline characteristics, particularly in smaller samples. Although reproducibility was ensured through the use of a fixed seed in SAS, future studies may benefit from using stratified or block randomization to enhance group comparability.

Lastly, the self-reported nature of gambling behaviors, while necessary for understanding personal habits and attitudes, introduces the potential for recall and social-desirability biases. The participants may underreport or overreport their gambling behaviors due to memory lapses or the desire to present themselves in a more socially acceptable light. To address these biases, future studies could incorporate objective measures or third-party reports to provide a more accurate assessment of gambling behaviors and the intervention’s impact.

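### The single-blind label names no blinded role, and the PGSI and MTM endpoints are rated by participants whose masking can be partial at best

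*Protocol article*

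**What the plan says.** Section 2.1 describes the design: "This study will implement a three-week, single-blinded educational randomized controlled trial (RCT"). The article does not name the blinded party or say how blinding is achieved.

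Section 2.6 separates the arms. Sessions are scheduled apart, "group-specific materials will be clearly labeled and distributed exclusively to each group", and participants are "instructed not to discuss session content with members of the other group".

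Section 2.7 gives the arms different content. For the experimental arm: "This intervention includes role-playing, psychodrama, journaling, and exploring recreational alternatives to address gambling behaviors". For the other: "The comparison group will participate in three knowledge-based sessions, each featuring lectures and presentations focused on gambling behavior". Section 2.4 adds contact for one arm only: "Additional reminders will be sent to the experimental group between sessions and after the intervention".

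Sections 2.9 and 2.13 fix the outcomes. PGSI and MTM scores come from a questionnaire that the participant completes at three time points, and both go into the mixed ANOVA. On the timing of the post-test, section 2.4 says: "The final session (Week 3) will consist of intervention activities followed by the post-intervention survey".

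Section 3.2 concedes that "the self-reported nature of gambling behaviors, while necessary for understanding personal habits and attitudes, introduces the potential for recall and social-desirability biases". It leaves objective or third-party measures to future studies.

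**The concern.** When the participant is the rater, blinding protects the measurement only if the participant is masked. Self-report error of equal size in both arms largely cancels in a between-group comparison. Error that differs by arm does not cancel, and the analysis cannot tell it from a treatment effect. Randomization does not remove it either, because it arises after allocation. Yet section 2.1 argues from randomization that observed differences can be put down to the intervention with confidence.

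The MTM scores deserve particular care. Section 3.2 relies on them to compensate for the 12-month recall window of the PGSI. They ask about readiness, confidence and commitment, which are the attitudes that the experimental sessions set out to build. A reader who sees the single-blind label may assume that both endpoints are shielded from arm awareness.

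**Working it through.** The plan gives no figure on blinding to reproduce. The check sets each possible meaning of the label against the procedures, then illustrates what an arm-dependent reporting difference would do to the planned test.

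**Meaning 1: the participant is blinded.** Section 2.6 tells participants that another group exists and gives them group-labelled materials. Sections 2.4 and 2.7 give one arm role-play, psychodrama, journaling and extra reminders, and the other arm lectures. Participants therefore know their own activities. They could still be unaware of which programme is under test, but the article describes no masking of the hypothesis, and section 2.9 says that consent makes the purpose of the study understood. Masking is at best partial.

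**Meaning 2: facilitators or data collectors are blinded.** No staff member rates the PGSI or the MTM scores, so this would leave the rating itself unprotected.

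**Meaning 3: the analyst is blinded.** This would have real value. It would protect decisions on who enters the per-protocol set (section 2.11) and whether the ANCOVA is triggered (section 2.13). It would not change the answers that participants gave.

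**Illustration.** Inputs from section 2.3: two groups, three time points, correlation ρ = 0.5, non-sphericity correction 1, alpha 0.05, and 20 per arm required, raised to 30 per arm. Both sizes are shown because section 2.11 describes an analysis restricted to compliant completers. Assumption, not in the document: no true effect, and a reporting difference of b SD between arms that is absent at pre-test and present at post-test and follow-up.

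- Between-arm difference over time: (0, b, b). Centred on its mean 2b/3: (−2b/3, b/3, b/3). Sum of squares: 4b²/9 + b²/9 + b²/9 = 2b²/3.
- Noncentrality of the group-by-time F test with n per arm: λ = (n/2) × (2b²/3) / (1 − ρ). With ρ = 0.5 this is λ = 2nb²/3.
- Degrees of freedom: 2 and 2(2n − 2), so 2 and 76 for n = 20, and 2 and 116 for n = 30.

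| b (SD, assumed) | λ, n = 20 | Significant, n = 20 | λ, n = 30 | Significant, n = 30 |
|---|---|---|---|---|
| 0 | 0 | 5.0% | 0 | 5.0% |
| 0.1 | 0.13 | 6.0% | 0.20 | 6.5% |
| 0.2 | 0.53 | 9.1% | 0.80 | 11.3% |
| 0.3 | 1.20 | 14.7% | 1.80 | 20.2% |
| 0.5 | 3.33 | 34.1% | 5.00 | 49.3% |

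The percentages are the probability that a noncentral F variable with these degrees of freedom and λ exceeds the central 5% critical value.

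**The case against.** Several parts of the case for the plan stand.

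- A condensed article may leave the blinded role to the full protocol. The omission alone is therefore not the point.
- The label may be true. If the analyst is blinded, the term is accurate and useful for analysis decisions. A reader might infer that the blinding is worthless or falsely claimed. The document does not support that.
- Neither the wording on the materials nor the consent text is shown. The labels may already be neutral. Telling participants of another group reveals that there are two groups, not which one is favoured. Both arms get three sessions of about 60 minutes on gambling, and an active comparator may reduce any reporting difference. A reader might infer that participants know they are in the favoured arm and that the bias must run towards it. That is plausible, but nothing in the article establishes it.
- The guest speaker in the final experimental session is part of the intervention, so a response to the speaker is partly a genuine effect. The post-test timing in section 2.4 is not stated as specific to one arm, and the eight-week survey takes place at a separate assessment session. The timing supports private completion. It does not show that the post-test is invalid.
- A reader might add the 30-day gambling questions to the affected endpoints. Section 2.9 presents them as baseline and screening items, and section 2.13 names only PGSI and MTM scores for the efficacy test.
- Visible arms and self-report are hard to avoid in behavioural education trials. Section 3.2 already discloses social-desirability bias, and section 2.5 already replaces names with ID codes.

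What the objection does not answer is that none of the possible meanings of the label masks the rater to session content, and that section 3.2 never considers bias that differs between the arms.

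**Conclusion.** The point holds in a limited form. The label leaves the blinded role open. Participants, who rate both efficacy endpoints, cannot be masked to their activities and are at most masked to the hypothesis. Blinding anyone else could guard analysis decisions but not the PGSI and MTM measurements. The stated limitation omits bias that may differ by arm, which is the form that would distort the comparison.

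The size and direction of any such bias cannot be derived from the document. For assumed shifts of 0.2 to 0.3 SD with no true effect, the group-by-time test would be significant in about 9% to 15% of trials at 20 per arm and 11% to 20% at 30 per arm. These figures rest on the invented shift, equal correlations of 0.5 and complete data. They show that a modest difference would matter, not that one exists. The conclusion does not call the trial invalid. It calls for an accurate description and some inexpensive protection.

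**What to change.** - **Section 2.1:** state which role is blinded and how. State that participants rate the outcomes and are not masked to session content. If the analyst is blinded, say so in the same sentence.
- **Section 2.6:** use neutral arm codes, for example Program A and Program B, on materials and in briefings, so that they do not show which programme is under test.
- **Section 2.4:** have the post-test and follow-up surveys completed privately under the existing ID code, away from the facilitator and the guest speaker.
- **Section 3.2:** state that self-report bias may differ by arm and that this limits the between-group conclusions on PGSI and MTM scores.

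The cost is relabelled materials, a possible small consent amendment and a slightly less favourable description of the design. Sample size, visits and the planned analysis are unaffected. These steps reduce cues and correct the description. They cannot mask participants to what they do in the sessions.
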